### Exclusion criteria

History of deep venous thrombosis and/or blood clotting disordersUncontrollable arterial hypertension (blood pressure > 160/100 mmHg) and dyslipidemia (total cholesterol > 220 mg/dl)History of stroke, heart failure, coronary ischemia, coronary arrhythmias, peripheral arterial disease, pulmonary diseases, and musculoskeletal problemsCurrent use of double antiplatelet agents: aspirin, Aggrenox, cilostazol, eptifibatide, ticlopidine, and tirofibanCurrent use of anticoagulants

### Termination criteria

Participants with serious adverse events or complications, who are not enabled to continue the trialParticipants withdrew their consent from the trial for any reasonParticipants lost to follow-up

### Ethics approval

This study was approved by the Ethical Committee of Xinhua Hospital Chongming Branch in November 2020 (approval no. CMEC-2020-KT-42). The study was registered in the Chinese Clinical Trial Registry (ChiCTR2100042803) in January 2021.

Demographic data (sex, height, age, household status, lifestyle habits, blood pressure, physical activity, and history of comorbidities), physical fitness results, questionnaire results, and signed consent forms will be gathered. The electronic data will be stored in an encrypted computer, and paper data will be stored at the project office in Xinhua Hospital Chongming Branch.

The investigators will perform the intervention in accordance with the protocol. Any questions about the protocol will be consulted with the head of Xinhua-Chongming hospital. If it involves modifications made to the protocol, the project leader will convene all research staffs to discuss and decide. Finally, the updated protocol will be reported to the ethics committee of Xinhua-Chongming hospital. All information of this protocol will be recorded on www.chictr.org.cn.

### Recruitment

Subjects will be recruited using three approaches: (1) the annual community physical examination in four communities in the Chongming District, (2) educational lectures and talks about sarcopenia at community centers, and (3) home visits in cooperation with community workers to check on the health of home-dwelling older people who do not participate in community activities regularly. The subjects will be screened on site by SARC-F, a valid screening tool for sarcopenia in Chinese older people [29] that assesses 5 components: strength, assistance in walking, rising from a chair, climbing stairs, and falls. The questionnaire has a score range from 0 (the best) to 10 (the worst) with a SARC-F score ≥ 4 points diagnosed as having a risk of sarcopenia. Subjects with a SARC-F score ≥ 4 points will complete the AWGS screening consisting of assessment of appendicular skeletal muscle mass index (ASMI) with a portable bioelectrical impedance analyzer system (Inbody, S10, Korean); handgrip strength with a hand dynamometer (HK-6000, Hengkang, China); and a 6-m walk to determine walking speed. A physician will conduct the examination and consultation on subjects who meet the inclusion criteria, and excludes subjects who meet the exclusion criteria.

### Randomization and blinding

Participants who meet the inclusion criteria and do not meet the exclusion criteria will be informed about the purpose and procedures of the study, what it will involve for them, and any risks involved in taking part as well as how to obtain more information about the study, low- and high-load resistance training and sarcopenia. After informed consent is obtained, subjects will be randomized into one of three groups: LRT-BFR, CRT, or control at 1:1:1 ratio. The randomization sequence, stratified by sex and age, will be generated and stored by a statistician who is not participating in the intervention and evaluation of the study, using SPSS version 20 statistical package (SPSS, Inc., USA). The random numbers and grouping assignments will be delivered in an encrypted electronic file to a research staff from another research for keeping this information. The therapists of this study will check the file and perform the intervention according to the grouping assignments. Except for therapists, all other participating staff, including the statistician, outcome assessors, and data managers will be blinded to the group assignment.

### Interventions

#### Group protocols

Before the group protocols begin, all subjects will complete a one-repetition maximum (1RM) strength test to assess their muscle strength and to determine the intensity for resistance training in training groups. In addition, they will complete three pre-intervention lessons with the resistance training exercises to familiarize themselves with the training sessions. Subjects randomized to the control group will receive health education sessions only. The researchers will record the attendance of each participant in each training session. And if a participant misses a scheduled training session, the session will be completed within the training week.

#### Resistance training program

Both resistance training intervention groups will receive three weekly resistance training sessions for 12 weeks with training intensities specific to their group assignment (see Table 2). Both groups will use Thera-band elastic bands to deliver the resistance exercises. Both groups will perform upper limb exercises (elbow extension and elbow flexion), followed by lower limb exercises (leg press and knee extension). The resistance training protocol of LRT-BFR will consist of 3 sets of 30-15-15 repetitions of each exercise, performed at an increased intensity from 20 to 30% 1RM by different Thera-band elastic bands. Subjects will have a 20-s rest interval between sets and a 30-s rest interval between exercises. The CRT group will perform 3 sets of 15 repetitions at 60% 1RM in the first 4 weeks, 3 sets of 12 repetitions at 65% 1RM in the second 4 weeks, and 3 sets of 10 repetitions at 70% 1RM in the third 4 weeks. They will have a 60-s rest interval between sets. The progressive resistance is also achieved by using Thera-band elastic bands with different tensions.

**Table 2 Tab2:** Details of the training protocol in the intervention groups

Weeks	Group	Sets	Repetitions	Intensity (%1RM)	Frequency (times/week)	Exercises	Interval between sets (s)
1–4	LRT-BFR	3	30, 15, 15	20	3	Elbow extension, elbow flexion, leg press, knee extension	30
	CRT	3	15	60	3		60
5–8	LRT-BFR	3	30, 15, 15	25	3	Elbow extension, elbow flexion, leg press, knee extension	30
	CRT	3	12	65	3		60
8–12	LRT-BFR	3	30, 15, 15	30	3	Elbow extension, elbow flexion, leg press, knee extension	30
	CRT	3	10	70	3		60

*LRT-BFR* Low-load resistance training with blood flow restriction, *CRT* Conventional high-load resistance training

#### Blood flow restriction

In the LRT-BFR group, blood flow restriction will be stimulated by inflating nylon cuffs connected to an inflator (TD312 Hokanson^TM^, Bellevue, USA) to the pressure as 50% of limb occlusion pressure (LOP). In order to provide personalized cuff pressure (mm Hg), technicians will measure the LOP of lower and upper limbs for each subject before the exercise intervention with a vascular Doppler probe (DV-600, Marted, São Paulo, Brazil). The assessment method of LOP will be as follows: while subjects are reclining, an ultrasound probe will be placed over the tibial and radial arteries to capture their auscultatory pulse in the lower and upper limbs, respectively. Remaining supine, the cuff will be placed at the most proximal part of the subject’s thigh for the lower limb resistance and at the most proximal part of the arm for the upper limb resistance. The cuff will be inflated to the point in which the auscultatory pulse is interrupted. The cuff pressure exerted at this time is referred to as the LOP. At this point, the subjects will then begin the LRT resistance training session. The exerted cuff pressure should not cause the subjects to feel pain or any discomfort during training and the pressure can be adjusted as needed according to the subject’s comfort. The cuff will remain inflated from the beginning to the end of each training session, including the rest intervals, and will be deflated immediately after the end of the last set.

#### Control group education sessions

The control group will meet once a week at the community center and receive a 60-min educational session on aging and health (see Table 3). Subjects will be instructed to maintain their usual lifestyles, and while some subjects may engage in some form of physical activity, they will not be provided an exercise program nor will they be encouraged to participate in a physical activity involving resistance training. To assess the subject’s usual physical activity levels, the Chinese version of the short form of the International Physical Activity Questionnaire (IPAQ) will be administered every week. The seven items in the short IPAQ provide an assessment of the duration and frequency of walking and moderate- and vigorous-intensity physical activity per week. The short IPAQ is scored by multiplying the duration in minutes per day, frequency in days per week, and a MET value of each activity (walking 3.3 METS, moderate-intensity 4.0 METS, vigorous-intensity 8.0 METS) to create MET-minute scores. The MET-minute scores are summed across activities to create a total MET-minute per week score for walking and moderate- and vigorous-intensity activities.

**Table 3 Tab3:** Details of education session topic in the control group

Week	Group	Education session topic	Frequency (times/week)
1–4	CG	Geriatric diseases and disease risk reduction	1
5–8	CG	Nutrition and physical activity for older people	1
9–12	CG	The importance of social support and care from friends, families, and communities	1

*CG* Control group

#### Nutritional intake

All the participants will maintain normal dietary habits during the 12-week intervention and follow-up period. They will record all their nutritional intakes including the amount of protein they took by 3-day dietary record (two weekdays and one weekend day in a week) per week on the notebook [30]. The weekly recording work is assisted and supervised by community works.

### Outcome measurements

The following measures will be conducted at baseline (0 week), after the 12-week intervention (12 weeks), and at follow-up (24 weeks).

#### Primary outcomes

##### Muscle strength in the lower limb

As the standard 1RM tests may be too difficult and induce skeletal muscle injury in older people with sarcopenia [31], the lower limb muscle strength will be assessed by an estimated 1RM of knee extension [32]. The estimated 1RM is calculated as follows: estimated 1RM (kg) = submaximal weight (kg)/(1.0278 − 0.0278 × maximal number of repetitions) [33]. According to the measurement method in the study of Brzycki et al. [31], the test is performed by subjects sitting on an extensor chair with a weight plate in kilograms [34]. The initial weight plate load is set at 45% of the body mass for female and 64% for male [35]. If they can repeat more than 10 times, they will be given a heavier weight to test. When the maximum number of repetitions is 10 or less, the weight is considered to be the submaximal weight. The maximal number of repetitions performed and submaximal weight will be used to calculate the estimated 1RM.

#### Secondary outcomes

##### Body composition

A bioelectrical impedance analyzer (Inbody S10, Korean) will be employed to measure body weight (BW), skeletal muscle mass (SMM), appendicular skeletal muscle mass (ASM), body fat mass (BFM), skeletal muscle mass index (SMI), and appendicular skeletal muscle mass index (ASMI). Of these indicators, the first four measures (BW, SMM, ASM, and BFM) are obtained directly through the test. The latter two indicators (SMI, ASMI) are obtained through calculation. According to methods described previously, SMI will be calculated as an SMI divided by the squared height (SMI = SMM/height^2^, kg/m^2^), and ASMI will be calculated as an ASM divided by the squared height (ASMI = ASM/height^2^, kg/m^2^) [1, 36].

##### Handgrip strength

The upper limb muscle strength will be assessed by the handgrip strength (HG) on each hand using a hand dynamometer (HK-6000, Hengkang, China). Subjects will be instructed to hold the dynamometer in a standing position, with the upper limb abducted at a 30-degree angle from the body. The maximum handgrip strength will be measured 3 times sequentially on each hand with the highest value in kilograms recorded [37].

##### Muscle performance

Muscle performance will be evaluated using the Short Physical Performance Battery (SPPB) test and the 6-m walk test. The SBBP incorporates performance in three tests: a standing balance test, a gait speed test, and a chair sit-stand test [38]. In the standing balance test, subjects will be required to stand and remain in three increasingly difficult positions (side-by-side, semi-tandem, and full-tandem stances) for 10 s each. In the gait speed test, the subjects will walk 8-feet at a normal pace for two times with the faster of two walks recorded. In the chair sit-stand test, the subjects will fold their arms across their chest and stand up and sit down five times as quickly as possible. The test will be timed from the starting sitting position to the final standing position. The score for each test ranges from 0 (unable to complete the test) to 4 (complete the test with no difficulty). The scores of the three tests will be summed with the highest total score of 12. For older people, SPPB scores are interpreted as follows: 10–12 = high performance, 7–9 = intermediate performance, and 0–6 = low performance [39]. The 6-m walk test requires subjects to walk at their usual speed for 6 m. Speed will be recorded with a timing device to record the total time it takes to walk 6 m at a usual speed. The test will be performed twice with the average of tests recorded [40].

##### Pulmonary function

Pulmonary function tests (forced vital capacity [FVC], peak expiratory flow [PEF], maximal inspiratory pressure [MIP], and maximal expiratory pressure [MEP]) will be conducted on a spirometer (Quark PFT ERGO, Italy) according to the standards of the American Thoracic Society (ATS) and European Respiratory Society (ERS) [41]. Each subject will be tested three times and the maximum value will be recorded.

##### Blood biomarkers and CVD risk factors

Following an overnight fast, study nurses will collect blood from the antecubital vein 48 h before the beginning of the 12-week intervention, 7 days after the end of the intervention, and 12 weeks after the end of the intervention, respectively. Enzyme-linked immunoassay (ELISA) will be used to determine the level of inflammatory biomarkers (IL-6, CRP, TNF-α), hormone (GH, IGF-1), growth factors (FST, MSTN), and CVD risk factors (fasting plasma glucose [FPG], total cholesterol [TC], triglycerides [TG], high-density lipoprotein cholesterol [HDL-C], and low-density lipoprotein cholesterol [LDL-C]). In addition, CVD risk factors also include systolic blood pressure and diastolic blood pressure.

##### Health-related quality of life

Health-related quality of life will be assessed using the validated Chinese version of the 36-item Short-Form Health Survey (SF-36). The SF-36 consists of 36 items, and it is a brief self-administered questionnaire designed to assess functioning and well-being in adults on eight health scales: physical functioning, role-physical, bodily pain, general health, vitality, social functioning, role-emotional, mental health, and reported health transition [42]. The score ranges from 0 to 100 with higher scores reflecting a better health-related quality of life.

### Sample size

The sample size was calculated with PASS (version 11.0). According to a previous study, lower limb muscle strength is the most relevant outcome to show the efficacy of blood flow restriction. Thus, it was used as the primary outcome for calculating sample size [43, 44]. According to the data used in the study by Brandner et al. [44], the expected mean changes in lower limb muscle strength were approximately 11% for the BFR training group, 16% for high-load resistance training, and 0% for the control group with a pooled standard deviation of 13%. This sets the estimated total sample size at 42 subjects (14 in each group) to meet 80% power and an alpha of 0.05. Considering the frailty of some older people with sarcopenia, up to a 20% dropout rate is expected. Therefore, the sample size is set at 51 subjects (17 in each group).

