As CRT is currently the conventional method to increase muscle strength, size, and performance in older people, it is important to compare the efficacy and safety of LRT-BFR with CRT and a non-exercise comparison group in older people with sarcopenia. Thus, the main aim of this study is to assess and compare the efficacy and safety of two different resistance training interventions (LRT-BFR vs. CRT) with a non-exercising control group on sarcopenia. Thus, the objectives of this study are to (1) systematically evaluate the efficacy of 12-week LRT-BFR and CRT on lower body muscle strength (primary outcome), body composition, muscle performance, pulmonary function, blood biomarkers, CVD risk factors, and quality of life (secondary outcomes) and (2) compare the efficacy and safety between LRT-BFR and CRT, LRT-BFR and CRT, and CRT and no-strength training group, to provide an effective and safe method for the management of sarcopenia.

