### Statistical analysis

The clinical and questionnaire results will be collected in this study. Among these results, results from the participants both seven clinical evaluations and one questionnaire will all be included in the data analysis. SPSS version 20 statistical package (SPSS, Inc., USA) will be used to analyze all data with *p* < 0.05 indicating statistical differences. Data will be analyzed for all participants in an intent-to-treat plan. Continuous data will be expressed as mean ± standard deviation (M ± SD), or median. For between-group comparisons of baseline characteristics, one-way analysis of variance (ANOVA) or Kruskal-Wallis tests will be used for parametric and non-parametric continuous data, respectively. The chi-square test will be used for categorical data.

According to the intention-to-treat principle, a linear mixed model will be used for analyzing the differences between the three interventions group over time on the outcome variables. Missing data will be assumed missing at random and handle by a linear mixed model by using maximum likelihood.

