The study also has some limitations. As a new training method, there are few studies that report the safety and potential adverse outcomes of LRT-BFR in older people, especially those with sarcopenia. Cook et al. [58] noted that the fatigue caused by LRT-BFR is similar or may even be higher than that caused by high-load resistance training. Although fatigue may have the potential to stimulate muscle growth, it can also reduce the compliance of resistance training in older people, especially those who are frail. Therefore, the fatigue level of subjects will be monitored closely during and after the training sessions with sessions modified as needed.

To date, although sarcopenia affects a large proportion of the population in the world, there are no pharmacologic agents to prevent or reduce its impact. Nor is there a consensus on the prevention and treatment of sarcopenia. Accordingly, the management of sarcopenia is still an unknown field. As a novel training method, LRT-BFR has the potential to make it easier for older people with sarcopenia to complete exercise training and achieve the same training effects as CRT in muscle mass and strength without increasing the risks of injury. Therefore, as a feasible alternative training method to CRT, LRT-BFR may be a potential training method to prevent the progression of sarcopenia.

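### The stated 80% power at 14 per group does not apply to either comparison involving LRT-BFR: about 16% against CRT and about 58% against control

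*Protocol article*

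**What the plan says.** All planning inputs are in the Sample size section of the protocol article. The expected changes in lower limb strength are "approximately 11% for the BFR training group" and "16% for high-load resistance training, and 0% for the control group", "with a pooled standard deviation of 13" per cent. The conclusion drawn is "This sets the estimated total sample size at 42 subjects (14 in each group) to meet 80% power and an alpha of 0.05". The section names the software ("The sample size was calculated with PASS (version 11.0"), but not the test or the comparison that was powered. An allowance for up to 20% dropout then raises 14 to 17 per group, 51 in total.

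The title sets LRT-BFR against CRT. The last paragraph of the Background makes that comparison, with a non-exercising control, the main aim. Objective (2) there is pairwise: "compare the efficacy and safety between LRT-BFR and CRT, LRT-BFR and CRT, and CRT and no-strength training group". One pair appears twice, and LRT-BFR against control does not appear in the list.

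The Statistical analysis section plans a linear mixed model for the three groups over time. The Discussion says that LRT-BFR has the potential to "achieve the same training effects as CRT in muscle mass and strength". The article gives no equivalence or non-inferiority margin.

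**The concern.** A reader who meets an unqualified 80% beside pairwise objectives will take it to cover those objectives, above all the title comparison. An overall test of three groups answers a different question: whether the groups differ at all. Under the planned means, that test is driven mainly by the 16-point gap between CRT and control, which says nothing about the new method.

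The planning assumptions themselves put LRT-BFR 5 points below CRT. If the trial has little chance of detecting that deficit, a non-significant difference is the expected result even when the deficit is real. The article also expresses the hope that the two methods perform alike, so the reader needs to know what such a result can and cannot show.

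**Working it through.** **Inputs** (Sample size section): means 11, 16 and 0; SD 13; alpha 0.05; 14 per group. Two-sided testing is assumed for the pairwise comparisons because the article does not state sidedness.

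**Step 1. Reproduce the plan's figure.** For a one-way three-group F test:

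- The grand mean is (11 + 16 + 0)/3 = 9. The squared deviations are 4 + 49 + 81 = 134.
- The noncentrality is λ = n × 134/13² = n × 0.793, on 2 and 3(n − 1) degrees of freedom.
- n = 13: λ = 10.31, critical F(2, 36) = 3.26, power 79.3%.
- n = 14: λ = 11.10, critical F(2, 39) = 3.24, power 82.6%.

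So 14 is exactly the smallest n that reaches 80%, which gives 42 in total as printed.

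**Step 2. Could 14 come from a pairwise test?** Unadjusted two-sided t tests at 80% power need:

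- LRT-BFR against CRT: 108 per group
- LRT-BFR against control: 23 per group
- CRT against control: 12 per group

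None is 14. One adjusted reading also first reaches 80% at 14: CRT against control at alpha 0.025 (80.4%). No such adjustment is stated, and that reading would not cover LRT-BFR either.

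**Step 3. Pairwise power at the planned size.** The standard error of a difference is 13 × √(2/n). That is 4.91 at n = 14 (df 26, critical t 2.056) and 4.46 at n = 17 (df 32, critical t 2.037). The noncentrality is the difference divided by the standard error.

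| Comparison | Difference | Noncentrality, n = 14 | Power, n = 14 | Power, n = 17 |
|---|---|---|---|---|
| LRT-BFR against CRT | 5 | 1.02 | 16.5% | 19.3% |
| LRT-BFR against control | 11 | 2.24 | 57.8% | 66.7% |
| CRT against control | 16 | 3.26 | 88.0% | 93.6% |

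The n = 17 column assumes no dropout. A 20% loss from 17 leaves 13.6, so 14 is close to the plan's own expectation.

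**Step 4. Precision.** The 95% confidence interval half-width for a pairwise difference is 2.056 × 4.91 = 10.1 points at n = 14 and 2.037 × 4.46 = 9.1 points at n = 17. At n = 14 that is twice the assumed 5-point difference and close to the whole 11-point LRT-BFR effect.

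**Step 5. Effect of an optional gate.** Suppose the pairwise tests are run only after a significant overall test (simulation at n = 14, one-way ANOVA, pooled variance). The powers are:

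- LRT-BFR against CRT: about 17%, hardly changed by the gate
- LRT-BFR against control: about 57%, against 59% without the gate
- CRT against control: about 81%, against 89% without the gate

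The ungated figures differ slightly from Step 3 because the variance is pooled over three groups.

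**The case against.** The calculation can be defended. Fourteen per group is right for a three-group F test, and the planned model compares all three groups, so sample size and analysis are broadly aligned. This stands: the arithmetic is sound for that test. The fault is that the 80% is left unqualified beside objectives it does not cover.

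The overall test is also an inference, because the article names none. That stands too, and the sponsor should confirm it. The conclusion does not depend on it, since no two-sided reading of 14 per group gives 80% for either LRT-BFR comparison.

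The mixed model might gain power by using the baseline. However, the SD of 13% is already given alongside mean changes, and no correlation is supplied from which to quantify a gain. For LRT-BFR against CRT to reach 80% at 14 per group, the SD would have to fall to about 4.5.

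A reader might infer three stronger points that the documents do not support:

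- **That the trial can support none of its comparisons.** CRT against control is a stated comparison and has about 88% power.
- **That the plan inflates the familywise error through three unprotected tests.** The article gives a general significance threshold and a mixed model but specifies no pairwise procedure. Order and adjustment are commonly left to an analysis plan.
- **That the authors will read non-significance as equivalence.** The Discussion states a potential, not a hypothesis or a decision rule.

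The duplicated pair in objective (2) is probably a slip, since the main aim just before it already includes the control group. It still needs correcting, because the pair it displaces is the direct efficacy test of the new method.

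**Conclusion.** The point holds as a misstatement of what the design can deliver. The 80% reproduces as the power of an overall three-group test. It does not apply to LRT-BFR against CRT (about 16%) or to LRT-BFR against control (about 58%), and full retention of 51 participants does not change that. Under the plan's own assumptions, the trial would miss the 5-point deficit about five times in six. With an interval of about ±10 points and no margin, a non-significant difference could not support the hope of equal effects.

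These figures rest on the article's means and SD, equal group sizes, two-sided 0.05 without adjustment, and a simple comparison of changes. That the overall F test was the one powered is inferred from the exact match.

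**What to change.** - **Sample size:** state that 80% refers to the overall three-group test, once the sponsor confirms this. Give the unadjusted pairwise powers at 14 per group: about 16% (LRT-BFR against CRT), 58% (LRT-BFR against control) and 88% (CRT against control).
- **Objective (2):** replace the duplicated pair so that the list reads LRT-BFR against CRT, LRT-BFR against control, and CRT against control.
- **Statistical analysis:** report LRT-BFR against CRT as an estimate with its 95% confidence interval. State that a non-significant result will not be taken as similarity or non-inferiority.

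The cost is wording, a less favourable power statement and a limit on what can be claimed for LRT-BFR against CRT. No participants are added.

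Gating the pairwise tests on the overall test is optional. It changes the test procedure and costs about 7 points of power for CRT against control. If it is adopted, the powers to print are about 17%, 57% and 81%; printing 88% beside a gate would be wrong.

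### The stated 80% power fits only an overall three-group test; on the same inputs LRT-BFR has about 59% power against control and 17% against CRT

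*Protocol article*

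**What the plan says.** The Sample size section of the protocol article takes lower limb strength as the primary outcome, on the ground that it best shows what blood flow restriction achieves. The expected mean changes are "approximately 11% for the BFR training group, 16% for high-load resistance training, and 0% for the control group", "with a pooled standard deviation of 13" (percent). From these it concludes: "This sets the estimated total sample size at 42 subjects (14 in each group) to meet 80% power and an alpha of 0.05". Because "up to a 20% dropout rate is expected", 17 per group (51 in total) are to be randomised. The section names no test, no contrast and no sidedness.

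The Background gives the main aim as a comparison of the two training methods, with a non-exercising control group. The second objective is to "compare the efficacy and safety between LRT-BFR and CRT"; as printed it lists that pair twice and then CRT against control. The Statistical analysis section plans a linear mixed model for differences between the three groups over time. No section gives power for any pair of groups.

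**The concern.** A single power figure, attached to three different means, can describe an overall test that the groups are not all alike. The questions this trial asks are narrower: does LRT-BFR improve strength over no training, and how does it compare with CRT? A test that the three means differ answers neither. Since CRT is assumed to have the largest gain and control none, that pair may carry most of the power.

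A reader who sees 80% power, beside an endpoint chosen to show the effect of blood flow restriction, will take it as power to show that LRT-BFR works. If it is not, a null LRT-BFR result may be read as adequately powered, and a significant overall result may be credited to LRT-BFR when it comes from CRT, the established method.

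**Working it through.** **Inputs.** From the Sample size section: means 11, 16 and 0; SD 13 (variance 169); alpha 0.05; 14 evaluable and 17 randomised per group. Assumed: two-sided pairwise tests, since sidedness is not stated.

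**1. Reproducing 14 per group.** For a one-way F test, the noncentrality is λ = n·Σ(mᵢ − m̄)²/SD², with 2 and 3(n − 1) degrees of freedom.
- m̄ = (11 + 16 + 0)/3 = 9; Σ(mᵢ − m̄)² = 2² + 7² + 9² = 134.
- n = 13: λ = 13 × 134/169 = 10.31, power 79.3%.
- n = 14: λ = 14 × 134/169 = 11.10, power 82.6%.

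So 14 is the smallest group size reaching 80% for the overall test, and 3 × 14 = 42 is reproduced.

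Pairwise two-sided t tests do not give 14: they need 12 (CRT vs control), 23 (LRT-BFR vs control) and 107 or 108 (LRT-BFR vs CRT, pooled or two-sample degrees of freedom). Normal approximations give 11, 22 and 107 two-sided, or 9, 18 and 84 one-sided. Bonferroni-adjusted t tests (alpha/3) give 16, 31 and 143.

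**2. Where the overall power comes from.** The shares of the 134 are control 81 (60%), CRT 49 (37%) and LRT-BFR 4 (3%).

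**3. Pairwise power on the same inputs.** Noncentral t, δ = d/(SD·√(2/n)), degrees of freedom 3(n − 1). At n = 14, SD·√(2/n) = 13 × √(2/14) = 4.91.

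| Contrast | d | δ at 14 | Power at 14 | Power at 17 |
|---|---|---|---|---|
| CRT vs control | 16 | 3.26 | 88.8% | 94.0% |
| LRT-BFR vs control | 11 | 2.24 | 58.8% | 67.6% |
| LRT-BFR vs CRT | 5 | 1.02 | 16.8% | 19.6% |

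The 17-per-group column assumes that nobody is lost. With two-sample degrees of freedom the values at 14 are 88.0%, 57.8% and 16.5%.

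Variants for the two LRT-BFR contrasts at 14 per group:
- one-sided 0.05: 70% vs control, 26% vs CRT;
- Bonferroni alpha/3, two-sided: 39–41% vs control, 8% vs CRT.

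No variant brings either contrast to 80%.

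**4. What a significant overall test says about LRT-BFR.** Suppose LRT-BFR does nothing, with means 0, 16 and 0. Then m̄ = 5.33, the sum of squares is 170.7, λ = 14 × 170.7/169 = 14.14 and power is 91.0%, above the 82.6% at the planned means.

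At the planned means, simulation (200,000 trials) shows that 31% of trials with a significant overall test at 14 per group, and 26% at 17, have a non-significant LRT-BFR vs control contrast.

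**The case against.** **The figure of 42 is correct for a three-group test.** Three means go into the calculation and one three-group model is planned, so sizing and analysis agree. That stands. The fault is not the sum but a power figure that is unlabelled and does not carry over to the aims. That the calculation was an overall test is inferred, as the only variant tried that fits. The shortfall for LRT-BFR does not depend on the inference.

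**The mixed model may be more precise than a t test.** It may, but the article gives no correlation from which to work out the gain. For 80% at 14 per group the effective SD would have to fall from 13 to about 10.1 for LRT-BFR vs control (about 11.2 at 17 per group). For LRT-BFR vs CRT it would have to fall to about 4.6, which modelling alone could not plausibly deliver.

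**Power for a difference from CRT may be the wrong quantity.** The article repeatedly suggests similar gains, for which a margin would be needed. This is fair, and 17% should be read as power to detect the assumed 5-point difference. No margin is given, and a non-significant difference at that power would not support similarity.

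**The misattribution risk is hypothetical.** The article nowhere says that a significant overall test will be reported as LRT-BFR efficacy. The 31% and 26% count true effects missed, not false credit, and the inert scenario departs from the planned means. Those figures illustrate what the overall test cannot show; the finding does not rest on them.

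**LRT-BFR vs control is absent from the second objective.** As printed it is, apparently by a slip. The contrast follows from the main aim and the first objective, and LRT-BFR vs CRT, the weakest one, is named outright.

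**Contrasts can be left to an analysis plan.** Detailed contrast rules can. The power statement is made in this article and is misleading as worded.

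**Conclusion.** The concern holds. The stated 80% is reproduced only as the power of an overall three-group test (82.6% at 14 per group), driven by CRT against control. It does not apply to LRT-BFR against control (about 59%, or 68% if all 17 per group are retained) or to LRT-BFR against CRT (about 17%, or 20%).

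These figures rest on the article's own means and SD, two-sided 0.05 tests without multiplicity correction, and an analysis of change scores with SD 13. A multiplicity correction would lower them. A more precise model could raise the first by an amount that the article does not allow one to calculate, but could not plausibly bring the second near 80%.

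**What to change.** Reword the Sample size section to say that 14 per group gives about 83% power for the overall three-group comparison only. Beside it, list the pairwise power on the same assumptions: about 89% for CRT vs control, 59% for LRT-BFR vs control and 17% for detecting the assumed 5-point difference between LRT-BFR and CRT. State the assumptions (two-sided 0.05, no multiplicity correction, 14 evaluable per group).

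Add that a significant overall test alone will not be reported as efficacy of LRT-BFR, and that this claim rests on the LRT-BFR vs control contrast with its confidence interval.

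The sample size, design and model stay as they are. The cost is text, and a less favourable power statement for the contrasts that matter most. For reference, 80% would need 23 per group for LRT-BFR vs control and about 107 for LRT-BFR vs CRT.
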